### Intervention

Patients will be randomly assigned to receive general anesthesia with either sevoflurane alone or propofol alone. Anesthesia will be maintained with approximately 1 minimum alveolar concentration (MAC) in the sevoflurane group; in the propofol group, anesthesia will be maintained with a continuous infusion of 2–4 μg/mL in a target- controlled infusion pump programmed with the Marsh pharmacokinetic model, using adjusted body weight, aiming to maintain a suitable level of hypnosis (bispectral index (BIS) 40–60) [26].

### Minimization of bias

Patients will be randomized using a computer-generated random number table, with an allocation ratio of 1:1. The allocation sequence will be implemented by a telephone call at the time of surgery. An investigator will collect data, and blood and adipose tissue samples will be coded so that the investigator evaluating the laboratory outcomes remains blinded to group allocation.

### Standard care

Patients assigned to both groups will receive intravenous fluids at a volume of 10–15 mL/kg total body weight (TBW) if possible [27, 28]. According to patient randomization, anesthesia in the TIVA with propofol group will be induced using propofol (1.5–2 mg/kg ideal body weight (calculated as height in cm – x, where x = 100 in adult men and 105 in adult women)) [29], whereas in the sevoflurane group, anesthesia will be induced using midazolam (0.05–0.15 mg/kg TBW) [29]. All patients will then receive alfentanil (15–20 μg/kg lean body weight (LBW), defined in men as 1.1 × (weight) − 128 × (weight / height)^2^ and in women as 1.07 × (weight) – 148 × (weight/height)^2^ [30] and rocuronium (1.2 mg/kg IBW)) [31]. Patients will receive a continuous infusion of remifentanil (0.1–0.4 μg/kg/min LBW) after induction of anesthesia and during surgery [31]. All patients will undergo neuromuscular monitoring with quantitative devices [32]. Patients will be extubated using sugammadex 2 mg/kg IBW if the train of four (TOF) is ≥ 2 responses or sugammadex 4 mg/kg IBW if TOF = 0 and the post-tetanic count (PTC) is ≥ 1 (33) [33].

After closure of the surgical incision, morphine (0.08 mg/kg IBW) will be administered intravenously [29]. Postoperative analgesia will consist of dipyrone (metamizole) 1 g every 6 h, ketoprofen 100 mg every 12 h or parecoxib 40 mg every 12 h, and tramadol 50–100 mg every 8 h or as rescue analgesia. Ondansetron (4 mg every 8 h) will be administered as prophylaxis for nausea and vomiting.

### Samples

Blood (15 mL) will be collected in heparinized tubes prior to induction of anesthesia (baseline), immediately after anesthetic induction (T1), and before extubation (T2).

Two small fragments of subcutaneous adipose tissue and visceral adipose tissue will also be sampled. Each fragment will measure 2 × 2 × 2 cm after excess blood vessels and connective tissue have been removed with the aid of a scalpel, and will be obtained from surgical specimens that would be discarded immediately following gastroplasty.

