Previous studies compared sevoflurane with propofol on performance, effectiveness, recovery from anesthesia, and bispectral index (BIS) recordings (a marker of possible intraoperative awareness) [18, 19], but have not evaluated the immunomodulatory potential of these anesthetics in obese patients.

Overall, in centers with distinct expertise, the 30-day mortality rate in bariatric surgery is low (0.1–2%) [20], as is the rate of major complications (3.6% after gastric bypass and 2.2% after sleeve gastrectomy) [21]. However, apart from major and early complications, minor complications can still occur in the days following surgery, which may increase hospital length of stay. The inflammatory process is involved in the perioperative period, in which it impairs wound healing and increases the risk of infection. To date, no study has evaluated which anesthetic agent is associated with the least inflammation and fewest complications in obese patients undergoing surgery.

Therefore, we designed the OBESITA trial to assess the immunomodulatory effects of anesthetics and inform future sample size calculations for studies evaluating sevoflurane versus propofol in obese patients undergoing bariatric surgery. Our hypothesis is that anesthesia with sevoflurane will result in a weaker inflammatory response to surgery than anesthesia with propofol [17, 22].

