### Postoperative data

The following clinical data will be evaluated within 24 h of surgery: vital signs (HR, NIBP, RR, and axillary temperature (AT)), complete physical examination, presence of organ dysfunction, visual analogue scale (VAS) score for pain, and postoperative complications (pulmonary infection, systemic inflammatory response syndrome, sepsis, septic shock, extrapulmonary infection, coma, acute myocardial infarction, acute renal failure, disseminated intravascular coagulation (DIC), gastrointestinal failure (GIF), and acute liver failure).

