### In vitro assays

#### Blood samples

Blood samples will be collected from all patients at baseline, T1, and T2. Heparinized tubes will be immediately centrifuged at 1500 × *g* for 5 min at 4 °C for separation of plasma and cells. These samples will be centrifuged within 6 h of collection. Plasma will be stored at − 80 °C until the time of analysis. The cell pellet will be used for monocyte and neutrophil isolation and evaluation, while plasma will be used later (after perioperative monitoring) for quantification of C-reactive protein (CRP), procalcitonin (PCT), IL-6, IL-10, and TNF-α levels.

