### Study endpoints

#### Primary

The primary endpoint is the difference in plasma levels of IL-6 when comparing patients anesthetized with sevoflurane versus propofol.

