
## Statistical analysis

Positive modulation of the IL-6 receptor and IL-6 expression in adipose tissue is known to occur in obesity [51, 83]. A convenience sample of 48 patients has been chosen on the basis of a study in which plasma IL-6 levels were compared before and after anesthesia in patients undergoing thoracic surgery with one-lung ventilation [84]. The sample size was calculated using G*Power 3.1.9.2 software (University of Dusseldorf, Germany), taking into account an effect size of 1.33, a two-sided test, and a ratio of 1. A sample size of 10 patients in each group will provide adequate power (80%), assuming α = 0.05, to detect at least an effect size of 33% difference in IL-6 levels in plasma samples collected immediately after induction of anesthesia and before extubation in obese patients anesthetized with sevoflurane or propofol (*p* = 0.05). Considering possible losses and to obtain even more significant results, we chose to increase the sample to 24 patients per group. Data will be tested for normality and variability. Comparison of the parameters of interest between participants in the sevoflurane and propofol groups will be performed by Student’s *t* test or the Wilcoxon test, as appropriate. Statistical significance will be accepted at *p* < 0.05. All analyses will be undertaken by an independent statistician, who will be blinded to group allocation.

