There are several patient-related (and thus nonmodifiable) factors associated with increased incidence of postoperative complications after bariatric surgery: male sex, preoperative BMI ≥ 60 kg/m^2^, open surgery, smoking within the last year, deep vein thrombosis, therapeutic anticoagulation, and serum albumin < 3.5 g/dL [91]. The duration and invasiveness of the surgical procedure may affect the inflammatory response, thus increasing the risk of bias [91], and will therefore be taken into account in this trial; these factors will be individually analyzed post hoc to isolate their interference with the outcomes of interest. The role of positive end-expiratory pressure (PEEP) in mechanical ventilation during general anesthesia for surgery remains uncertain. An ongoing randomized clinical trial is testing two different levels of PEEP: 4 cmH_2_O without recruitment maneuvers versus 12 cmH_2_O with recruitment maneuvers [35, 92]. In the present trial protocol, a PEEP of 5 cmH_2_O is suggested based on a secondary analysis of the international multicenter LAS VEGAS study, restricted to obese patients [93].

To our knowledge, only one prospective study has compared the effect of anesthesia with sevoflurane on inflammation to that of TIVA with propofol, in 54 adults undergoing thoracic surgery with one-lung ventilation [22]. The authors observed that the increase in inflammatory mediators such as TNF-α, IL-6, and monocyte chemoattractant protein 1 (MCP-1) was significantly blunted in the sevoflurane group. Sevoflurane was also associated with fewer postoperative adverse events [22]. A randomized controlled trial of 5400 patients, which compared volatile anesthetics to TIVA for elective cardiac surgery, showed that anesthesia with a volatile agent did not result in a significantly lower 1-year mortality rate compared to TIVA [94].

Moreover, in the experimental setting of obesity, a 1-h infusion of propofol resulted in increased airway resistance, atelectasis, and pulmonary inflammation mediated by increased TNF-α and IL-6 in lung tissue, with depletion of antioxidative enzymes [17]. Based on this evidence, we hypothesize that anesthesia with sevoflurane will result in a weaker inflammatory response compared to anesthesia with propofol.

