This study is the first step toward choosing an anesthetic strategy that is capable of reducing systemic inflammation in obese subjects (i.e., patients with chronic inflammation) undergoing laparoscopic bariatric surgery. Some studies have compared sevoflurane with propofol, but have focused on clinical consequences, such as intraoperative mean arterial pressure, eye opening, extubation, recovery from anesthesia, postoperative pain, and incidence and severity of postoperative nausea and vomiting (PONV) [18, 95], without understanding the mechanisms associated with clinical improvement.

Sevoflurane, a low-solubility inhaled anesthetic, is the first-line anesthetic agent of choice in Brazil. It has been shown to have a cardioprotective effect, preventing myocardial ischemia and arrhythmias [96], even though like other anesthetic agents it may cause hypotension [97]. A study determined that the minimal alveolar concentration (MAC) for sevoflurane needed to maintain the BIS at < 50 in morbidly obese patients undergoing bariatric surgery [98] was 1.8–1.6%, higher than those values previously reported in normal adult patients (0.97%; 95% CI 0.89–1.1%) and lower than those reported in children (2.8%; 95% CI 2.7–3.1%), which justifies the minimal MAC of 1.0 defined for this protocol. Moreover, a double-blind randomized controlled trial in superobese patients (BMI > 50 kg/m^2^), in which the performance, effectiveness, and recovery from anesthesia was compared for sevoflurane versus propofol in combination with remifentanil, showed that although both propofol and sevoflurane provided adequate general anesthesia, sevoflurane may be preferable in the superobese due to superior hemodynamic stability and faster recovery [18].

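### T2, the only blood sample after incision, is tied to extubation: its timing is not controlled, and the trial can speak only to the intraoperative IL-6 response

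*Protocol article*

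**What the plan says.** **Sampling.** The Samples section lists a baseline draw before induction, then "immediately after anesthetic induction (T1), and before extubation (T2". The assay section repeats it: "Blood samples will be collected from all patients at baseline, T1, and T2". No clock time, interval from incision or sampling window is given for T2.

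**Endpoint.** The Primary section names no time point: "The primary endpoint is the difference in plasma levels of IL-6 when comparing patients anesthetized with sevoflurane versus propofol". The Statistical analysis section bases the sample size on "IL-6 levels in plasma samples collected immediately after induction of anesthesia and before extubation in obese patients", that is, on T1 and T2. The planned comparison is an unadjusted Student's t or Wilcoxon test.

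**Hypothesis.** The Background states: "Our hypothesis is that anesthesia with sevoflurane will result in a weaker inflammatory response to surgery than anesthesia with propofol". The closing paragraph of the Discussion again frames the aim as a weaker inflammatory response in patients having this surgery, with IL-6 as its marker.

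**After surgery.** The Postoperative data section begins "The following clinical data will be evaluated within 24 h of surgery" and lists vital signs, examination, organ dysfunction, pain and complications. It lists no cytokine measurement.

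**Duration.** The Discussion accepts that "The duration and invasiveness of the surgical procedure may affect the inflammatory response, thus increasing the risk of bias". It says these factors will be taken into account, by post hoc analysis. The Measurements section records duration of surgery but no time from incision to T2.

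**The concern.** Baseline and T1 both precede the incision, so any IL-6 response to surgery that the trial can detect in blood rests on T2. Two problems follow.

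1. **The anchor.** Extubation comes after randomization, and its timing depends partly on emergence, which the randomized agents can influence. Randomization balances the length of the operation in expectation, but it does not balance an interval that the treatment may change. If IL-6 is moving at that point, samples drawn at different times after incision give different values even when the drugs do not differ. Blinded assays do not remove this. The limitations paragraph says that processes able to influence the primary outcome are strictly controlled; for sample timing, no such control is stated.

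2. **The scope.** Nothing is measured in blood after T2. A difference at T2 would not show that the later response is weaker, and no difference at T2 would not exclude a later one. Neither result reaches the response to surgery as the Background words it.

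**Working it through.** **Step 1. The plan's own figure.** Inputs (Statistical analysis): effect size d = 1.33, two-sided α = 0.05, ratio 1, 10 per group, 80% power. Two-sample t test, noncentrality = d × √(n/2):

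- n = 10: 1.33 × √5 = 2.97 on 18 df, power 80.3% (n = 9 gives 75.5%). The figure of 10 is reproduced.
- n = 24: 1.33 × √12 = 4.61 on 46 df, power 99.5%.

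This calculation does not depend on when T2 is taken, so it neither supports nor weakens the point.

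**Step 2. Which samples can carry the response.**

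| Sample | Anchor | After incision? |
|---|---|---|
| Baseline | before induction | no |
| T1 | just after induction | no |
| T2 | before extubation | yes |
| Later | none planned | – |

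**Step 3. A gap between arms.** The documents give no IL-6 kinetics, no SD and no extubation times, so every input here is an assumption: doubling time D = 0.5–2 h around T2, SD of log IL-6 = 0.6–0.9, 24 per arm, no true drug effect. If one arm, either one, is sampled g minutes earlier:

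- spurious ratio = 2^(g/D), with D in minutes
- spurious standardized difference = ln(ratio) / SD
- false-positive rate = power of the two-sided t test at that difference

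| Gap | Ratio | False-positive rate (nominal 5%) |
|---|---|---|
| 5 min | 2^(5/120) = 1.03 to 2^(5/30) = 1.12 | 5.1–10.0% |
| 10 min | 2^(10/120) = 1.06 to 2^(10/30) = 1.26 | 5.5–25.7% |
| 15 min | 2^(15/120) = 1.09 to 2^(15/30) = 1.41 | 6.2–50.0% |

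A middle case, 10 minutes with doubling every 60 minutes: ratio 2^(10/60) = 1.12, ln = 0.116, standardized difference 0.116/0.9 = 0.13 to 0.116/0.6 = 0.19, false-positive rate 7.2–10.0%.

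**Step 4. Spread between patients, with no gap between arms.** Variance multiplier = 1 + [(ln 2 / D) × SD of time]² / SD², assuming an SD of time to T2 of 20–45 min and D = 1–2 h:

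- Low end (D = 2 h, 20 min, SD 0.9): (0.347 × 0.333)² / 0.81 = 0.016, about 2% more variance.
- High end (D = 1 h, 45 min, SD 0.6): (0.693 × 0.75)² / 0.36 = 0.75, 75% more variance.

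This part adds noise, not bias.

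**The case against.** **Timing may matter little.** Randomization balances operation length, which is recorded, and the Discussion promises to analyze it. In the middle case the artefact is 0.13–0.19 SD against a planned effect of 1.33. Much of this stands: spread between patients is mainly noise, and a gap of a few minutes does little harm. But duration of surgery does not capture the interval from closure to T2, which is the part that treatment can affect, and the handling is only post hoc.

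**The article is condensed.** The schedule figure is not shown, and a fuller protocol may define T2 more tightly. If T2 is in practice drawn at closure, the mechanism between arms largely disappears. That is fair. But the anchor is stated consistently in the article, and it is the wrong kind of event for this purpose.

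**Stopping at extubation is defensible.** The trial targets anesthetic effects and calls itself a pilot. After surgery, patients receive dipyrone with ketoprofen or parecoxib (Standard care), which could cloud a later sample, although the protocol does not give this as its reason. This stands. It is why a 24 h sample, which a reader might expect as the remedy, is a trade-off and is not asked for here.

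**A stronger reading is tempting.** The Discussion cites a trial concluding that "sevoflurane may be preferable in the superobese due to superior hemodynamic stability and faster recovery". A reader might infer that T2 comes earlier with sevoflurane and so tilts the result toward the hypothesis. The documents do not support this. That trial enrolled patients with BMI > 50 kg/m², while this one admits BMI ≥ 35. No minutes and no extubation times are given, and recovery may include the period after extubation. Here only the sevoflurane arm is induced with midazolam, which leaves the direction open.

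**Conclusion.** The point holds in two parts.

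First, T2 is the only blood sample after incision, and its anchor follows randomization and may depend on treatment. Time from incision to T2 therefore varies between patients and could differ between arms. The size of any bias is unknown: on the assumptions above it runs from negligible (5.1% false positives) to serious (50.0%, only at a 15-minute gap with the fastest assumed rise and the smaller SD). Its direction is not established.

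Second, with no later cytokine sample, the data support a statement about intraoperative IL-6 and nothing wider. This part needs no assumption about kinetics. How much of the IL-6 response comes after T2 would need one, so the documents do not show that T2 captures only a small share of it.

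A reader might also set the spurious ratios against the 33% difference named in the Statistical analysis section. That comparison is not safe: the calculation there used a standardized effect of 1.33, and no SD is given to link the two.

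The change is worth making because it removes a possible treatment-dependent timing bias at almost no cost.

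**What to change.** 1. Define T2 in both arms as a draw at one surgical event that precedes emergence: the end of skin closure. This changes the moment of sampling only; anesthetic and analgesic management stays as it is.
2. Record the clock times of incision and T2 for each patient, and report minutes from incision to T2 by arm. Variation from operation length will remain, but it is balanced in expectation and becomes visible.
3. Word the primary conclusion, and the matching statements in the Background and the closing paragraph of the Discussion, as the intraoperative IL-6 response.

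Cost: one sampling instruction, two recorded times per patient and some wording. No extra blood, assays or patients.

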### Mechanical ventilation

Patients from both groups will be mechanically ventilated in pressure-controlled mode, with a tidal volume (V_T_) of 5–7 ml/kg IBW, respiratory rate (RR) adjusted to maintain arterial partial pressure of carbon dioxide (PaCO_2_) between 36 and 44 mmHg, and a positive end-expiratory pressure (PEEP) of 5 cmH_2_O [34]. The inspired fraction of oxygen (FiO_2_) will be adjusted to maintain oxygen saturation of hemoglobin (SaO_2_) > 95% (0.4–0.5).

### Rescue strategies for intraoperative hypoxemia

Based on the protocol used in the PROBESE trial [35], if oxygen saturation falls to 92% or below, factors such as increased airway resistance, presence of intrinsic PEEP, hemodynamic instability, and ventilator malfunction should be excluded.

Initially, FiO_2_ should be raised gradually. Elevation of PEEP is restricted to more severe cases, when hypoxemia persists with FiO_2_ = 1.0. In this case, PEEP is gradually increased to 7 cmH_2_O. Alveolar recruitment maneuvers should be performed if SaO_2_ remains ≤ 92% [35].

Anesthesiologists may deviate from the ventilation protocol at any time if concerns about patient safety arise. PEEP may be modified at the anesthesiologist’s discretion.

### Measurements

The following ventilatory parameters will be measured at three time points - after anesthetic induction (approximately 10 min), after induction of pneumoperitoneum (approximately 20 min), and at the end of surgery: minute ventilation, RR, V_T_, peak and plateau pressures, PEEP, static and dynamic compliance, FiO_2_, and SaO_2_.

Arterial blood gases and hemoglobin level will be measured immediately after induction of anesthesia and before extubation.

Heart rate (HR) and noninvasive mean blood pressure (NIBP) will be measured throughout the procedure. The duration of surgery, the time before and after pneumoperitoneum, intra-abdominal pressure throughout the procedure, and the volume insufflated to achieve pneumoperitoneum will also be recorded.

### Postoperative data

The following clinical data will be evaluated within 24 h of surgery: vital signs (HR, NIBP, RR, and axillary temperature (AT)), complete physical examination, presence of organ dysfunction, visual analogue scale (VAS) score for pain, and postoperative complications (pulmonary infection, systemic inflammatory response syndrome, sepsis, septic shock, extrapulmonary infection, coma, acute myocardial infarction, acute renal failure, disseminated intravascular coagulation (DIC), gastrointestinal failure (GIF), and acute liver failure).

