#### Secondary

The secondary endpoints are (1) the differences in levels of other proinflammmatory and anti-inflammatory mediators in blood, subcutaneous tissue, and visceral adipose tissue, namely (a) inflammatory mediators associated with neutrophils: metalloprotease (MMP)-2 [36–38], MMP-9 [36], CXCR2 [39], IL-12 [40], CCL3 (macrophage inflammatory protein (MIP)-1α) [41–44], CCL2 (MCP1) [44], IL-1β [45], TNF-α [46], NRF2 [47, 48], (b) mediators associated with macrophages: proinflammatory (IL-1β, CD40 [49], CD80 [50]), M1 phenotype markers (TNF-α, IL-6 [51–53], iNOS [54–56]), anti-inflammatory (IL-1 receptor antagonist (IL-1RA) [57–59], NrF2), M2 phenotype markers (CD163 [60, 61], CD206 [62], arginase [63, 64], IL-10 [65], transforming growth factor (TGF)-β1 [66–68]), and (c) mediators associated with cell death pathways (BCL2-associated X (Bax), bcl2 [69, 70], caspases 3 and 9 [71–73]); (2) intraoperative complications: (a) hypoxemia (PaO_2_/FiO_2_ ratio < 300), (b) hypotension (systolic blood pressure < 90 mmHg), (c) bradycardia (heart rate < 50 bpm), (d) unexpected need for intensive care unit (ICU) admission or readmission, (e) length of hospital stay, (f) number of days at home in the first month after surgery, and (g) postoperative complications: pulmonary infection (defined as new or progressive radiographic infiltrate and at least two of the following criteria - antibiotic treatment, axillary temperature > 38 °C, leukopenia (WBC < 4000 cells/mm^3^) or leukocytosis (WBC > 12,000 cells/mm^3^), and/or purulent secretions); sepsis (defined as suspicion or certainty of infection and an acute increase ≥ 2 points in the Sequential Organ Failure Assessment Score (SOFA) in response to an infection, representing organ dysfunction); septic shock (defined as sepsis plus need for vasopressor to maintain mean blood pressure > 65 mmHg plus lactate > 2 mmol/L [18 mg/dL] after adequate volume resuscitation [74–76]); extrapulmonary infection (of the operative wound or any other infection); coma (Glasgow Coma Scale < 8 in the absence of therapeutic sedation); acute myocardial infarction (according to the universal definition thereof [77]); acute kidney failure (according to the risk, injury, failure, loss, end-stage renal failure (RIFLE) criteria classification system [78]); DIC (according to the International System for the Evaluation of Thrombosis and Hemostasis for DIC [79]); GIF (defined according to the GIF score [80]); acute liver failure (defined as a ratio of total bilirubin on the 5th postoperative day to the 1st postoperative day > 1.7 plus a ratio of international normalized ratio (INR) on the 5th postoperative day to the 1st postoperative day > 1.0 or presence of hepatic encephalopathy and INR > 1.5) [81, 82].

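### Postoperative complications are evaluated within 24 h of surgery, but the main limb of acute liver failure needs day-5 values and later infections would be missed

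*Protocol article*

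**What the plan says.** Two sections of the protocol article govern the postoperative complications.

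- **Postoperative data** sets the timing: "The following clinical data will be evaluated within 24 h of surgery". The sentence covers vital signs, physical examination, organ dysfunction, VAS pain and a named list of complications. The list includes pulmonary and extrapulmonary infection, sepsis and septic shock, and ends with "disseminated intravascular coagulation (DIC), gastrointestinal failure (GIF), and acute liver failure".
- **Study endpoints, Secondary** gives the definitions. The first limb is "acute liver failure (defined as a ratio of total bilirubin on the 5th postoperative day to the 1st postoperative day > 1.7", combined with an INR ratio "on the 5th postoperative day to the 1st postoperative day > 1.0". The second limb is "or presence of hepatic encephalopathy and INR > 1.5". The same section lists length of hospital stay, unexpected ICU admission or readmission, and "number of days at home in the first month after surgery".

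The Background adds that "minor complications can still occur in the days following surgery, which may increase hospital length of stay". It also says that the trial should inform sample size calculations for later studies, and the end of the Discussion looks ahead to a larger trial on mortality and morbidity.

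**The concern.** One section says when complications are evaluated and another says what counts as a complication, and for acute liver failure the two cannot both be followed. A team that stops at 24 h never obtains the day-5 values. A team that takes the day-5 values has left the stated window.

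The window matters for the infections too. Pulmonary, wound and other infections are on the same 24 h list. Under that rule a patient whose infection appears on day 3 is recorded as free of infection. The article's own rationale is that perioperative inflammation impairs healing and raises the risk of infection, and that some complications come days later. The stated window would leave out part of what the endpoint is meant to capture.

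At stake are the complication counts. Rates cut off at 24 h would be too low in both arms and would be carried into the planning of the next trial. A day-5 sample that was not taken cannot be recovered afterwards.

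**Working it through.** No calculated figure in the article bears on this point. Its one calculation, the sample size for IL-6, is independent of the complication window. The check is a comparison of time windows.

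**Inputs**

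| Item | Value | Where |
|---|---|---|
| Evaluation window for listed complications | 24 h | Postoperative data |
| Liver failure, limb 1 | day-5/day-1 bilirubin ratio > 1.7 and day-5/day-1 INR ratio > 1.0 | Secondary |
| Liver failure, limb 2 | encephalopathy and INR > 1.5 | Secondary |
| Days at home | first month | Secondary |

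**Step 1: liver failure, limb 1.** Day 5 is at about 5 × 24 = 120 h. The gap to the end of the window is 120 − 24 = 96 h. If the day of surgery were counted as day 1, day 5 would be at about 4 × 24 = 96 h and the gap would be 96 − 24 = 72 h. On either count the numerators of both ratios lie well outside the window, so limb 1 cannot be evaluated there.

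**Step 2: liver failure, limb 2.** This limb needs no day-5 value and can be met within 24 h. The endpoint therefore does not vanish; it shrinks to its second limb.

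**Step 3: infections.** Their definitions in the Secondary section carry no day count, so the 24 h sentence is the only timing the text states for them. An onset after 24 h is outside it and would be counted as no event.

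**Step 4: follow-up implied elsewhere.** Days at home in the first month needs information to about 30 × 24 = 720 h, which is 720 − 24 = 696 h beyond the window. The trial thus already intends to learn about patients well after 24 h, and a longer complication window would not need a new follow-up period.

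**Step 5: direction and size of the bias.** Omitting events after 24 h can only lower the counts, and it does so under the same rule in both arms. The article does not say what share of events appears by 24 h, so the size cannot be calculated. For scale only, the Background gives major-complication rates of 2.2% (sleeve gastrectomy) and 3.6% (gastric bypass). In 48 patients these give 48 × 0.022 = 1.06 and 48 × 0.036 = 1.73 expected events. The probability of none is (1 − 0.022)^48 = 34% and (1 − 0.036)^48 = 17%. These rates come with no definition or time window and do not map onto the listed complications.

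**The case against.** The strongest reply has four parts.

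1. **The sentence does not say that nothing is collected later.** This is correct. A reader might infer that complications are evaluated only within 24 h, or that length of stay, days at home and ICU admission or readmission cannot be obtained. The document does not support that. Those three endpoints are not in the 24 h list, and an unexpected ICU admission can occur within 24 h. The article does not describe how they are collected, but the schedule figure is not shown and a condensed article may leave this to the full protocol. What stands is narrower: the complications that are in the list have one stated window, and it conflicts with a definition in the same article. If the schedule figure shows later assessments, it disagrees with the text and the wording still needs repair.
2. **Liver failure has a second limb.** This is also correct, and it limits the contradiction to the ratio limb. Losing one of two limbs still changes which patients count as events.
3. **The Background speaks of minor complications in the later days, whereas much of the list is serious.** This is fair. That sentence does not show that sepsis or infarction will mostly come late. It does show that the authors expect events after the first day, and wound infection is within the listed extrapulmonary infections.
4. **The consequences are small.** The primary endpoint is plasma IL-6, with the last sample taken before extubation, so it is untouched. The trial is a pilot, the window is the same in both arms, and with one or two expected major events no window would give a precise rate. This stands and sets the severity. It does not remove the contradiction.

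**Conclusion.** The point holds as an inconsistency in the secondary endpoints, of moderate severity. The 24 h evaluation and the day-5/day-1 ratios for acute liver failure cannot both be followed; the gap is about 96 h (72 h on the shorter day count). Read plainly, the same window also counts infections after day 1 as absent. Complication rates would be biased low in both arms; nothing shows a bias in favour of one arm, and the amount cannot be derived from the document. The IL-6 comparison is not affected.

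This rests on two readings: that the 24 h phrase governs every item in its sentence, including the complications, and that the liver failure definition consists of two alternative limbs, of which only the first needs day-5 values.

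**What to change.** - Keep the 24 h evaluation for vital signs, physical examination and VAS pain.
- State one longer ascertainment window for the complications defined under Secondary, and use it in the Postoperative data section, the Secondary section and the schedule figure. One option is chart review to discharge plus the one-month follow-up that days at home already requires.
- Reconcile the acute liver failure endpoint: either schedule the day-1 and day-5 bilirubin and INR that the definition already calls for, or drop the ratio limb and keep encephalopathy with INR above 1.5. The article gives no expected length of stay, so the team should check whether patients will still be in hospital on day 5 before choosing.

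The cost is some extra chart review and a few more items at follow-up, plus the day-1 and day-5 tests if the ratio limb is kept. If it is dropped, the endpoint becomes narrower and the report should say so. The change should be made before data collection, because a missed day-5 sample cannot be replaced.
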